### Adapting clinical guidelines to a new drug landscape

Clinical guidelines in BC had previously regarded SROM as a third-line treatment behind buprenorphine/naloxone and methadone but updated their guidance in 2023, in response to rising overdose death rates across the province, to remove the tiers and advise collaborative treatment selection based on client preferences, clinical judgement and contextual circumstances.[6] Guidance for SROM is largely based on clinical consensus and expert opinion due to overall limited evidence to support decision-making.[6] This client-centered shift acknowledges that prior experiences with OAT often shape future treatment decisions. SROM may be an alternative option for individuals who have experienced negative outcomes with other OAT medications, such as incomplete elimination of withdrawal with buprenorphine/naloxone, or intolerable side effects with methadone, including sedation, emotional blunting, or cardiac risks such as QT prolongation.[11] Individuals with contraindications to methadone, including ventricular arrhythmias or concurrent use of QT-prolonging medications, may particularly benefit from SROM as the medication does not affect the QT interval.[11] Moreover, frequent or early switching between OAT options is often a signal of suboptimal treatment fit, whether due to poor tolerability, inadequate therapeutic response, or individual treatment goals not being met.[6,11]

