### Statistical analysis

We will adjust for all baseline covariates to estimate the initiator effect as hazard ratios, differences of cumulative incidence (risk) at 24 month, and risk curves using a marginal structural Cox proportional hazard regression model (MSM) with inverse probability of treatment weighting.[71,72]. For the per-protocol analysis, additional time varying confounding will be adjusted via censoring weights to mitigate selection bias from artificial censoring due to receipt of dose below key benchmark, treatment switching, violation of eligibility criteria including initiating pregnancy, incarceration, or treatment taper. However in the ‘clone-censor-weight’ approach for the sub-population (ix) and (x), we will not artificially censor for the violation of dosing benchmark and will estimate the artificial censoring weights conditional on their covariate history. Sandwich variance estimates will be used to compute the 95% compatibility (confidence) intervals for the adjusted hazard ratios,[73] while 500 bootstrap samples (with replacement) would be used to compute the compatibility intervals for risk differences and compatibility curves for risk curves.[74] We will apply high-dimensional propensity score (hdPS) and instrumental variable (IV) approaches for the initiator analysis as sensitivity analyses.[75,76] While the MSM and ‘clone-censor-weight’ approaches will target the marginal treatment effect, the IV analysis will estimate a local average treatment effect among compliers, i.e., individuals who would be prescribed the treatment preferred by treating physician or facility (see details in IV estimation section later). We will use SAS version 9.4 to prepare analytic data and conduct the statistical analysis using the SAS and R version 4.5.0.

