### IV estimation

We will apply IV estimation for initiator analysis as a sensitivity method to address potential uncontrolled confounding. Given the lack of established IV methods for multi-category exposures in time-to-event analyses, we will define a binary exposure: SROM versus either methadone or buprenorphine/naloxone. Two candidate IVs will be tested: (a) prescriber-level preference for SROM and (b) facility-level preference for SROM, both measured among OAT clients in the six months prior to time zero.[80] The validity of the IV relies on four key assumptions. First, the relevance assumption will be tested using a logistic regression model to assess the association between the IVs and the exposure while adjusting for individual- and prescriber-level characteristics. The exclusion restriction and exchangeability cannot be directly verified, so their plausibility will be assessed through expert clinical input from our scientific advisory committee. Additionally, we will evaluate bias due to omitted measured covariates by comparing non-IV and IV analyses.[81] The assumption of homogeneity defines whether the IV-exposure association remains consistent across measured confounders of the exposure-outcome association.[82] The monotonicity assumption requires that there are no “defiers”, i.e., individuals who would always receive opposite treatment to that assigned by IV, and is expected to hold trivially in this context since OAT initiation with SROM is largely determined by prescriber or facility preference rather than individual choice. Since homogeneity and monotonicity cannot be empirically tested, their validity will be assessed through expert consultation.[80,83] To estimate the local average treatment effect, we will apply a two-stage residual inclusion (2SRI) approach.[84,85] In the first stage, a logistic regression approach will model the exposure as a function of the IV and selected covariates, generating residuals that account for uncontrolled confounding. These residuals will be incorporated into a Cox-PH model alongside the exposure and selected covariates. From this fitted model, we will estimate hazard ratios, risk differences, and risk curves. Compatibility intervals and curves will be computed using the approach described earlier.

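### The IV section calls homogeneity untestable although its own definition can be tested, and its reason for monotonicity supports relevance, not the absence of defiers

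*Protocol article*

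**What the plan says.** The protocol article, section IV estimation, reduces the comparison to two groups: "we will define a binary exposure: SROM versus either methadone or buprenorphine/naloxone". The candidate instruments are the prescriber's and the facility's preference for SROM, taken from their OAT clients over the preceding six months. Relevance will be tested with a logistic model, and the first stage of the two-stage residual inclusion method is also logistic.

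On the remaining assumptions the section makes three statements:
- Homogeneity: "The assumption of homogeneity defines whether the IV-exposure association remains consistent across measured confounders of the exposure-outcome association".
- Monotonicity: it "is expected to hold trivially in this context since OAT initiation with SROM is largely determined by prescriber or facility preference", as opposed to the client's own choice.
- Both: "Since homogeneity and monotonicity cannot be empirically tested, their validity will be assessed through expert consultation".

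The Statistical analysis section states the target without qualification: "the IV analysis will estimate a local average treatment effect among compliers".

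**The concern.** There are two separate problems.

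First, homogeneity is defined with observed quantities only, and the same paragraph then says that no data can speak to it. Expert opinion is put in place of a check that the planned model can provide.

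Second, the reason given for monotonicity does not bear on it. If preference largely drives who starts SROM, the instrument is relevant. Monotonicity is a different requirement: no client would receive SROM under a lower preference and another drug under a higher one. The complier label rests on that requirement, and the article attaches no condition to the label.

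At stake is how one sensitivity analysis is read. The Subgroup and sensitivity analyses section puts relevant findings from each approach in a forest plot. A complier estimate with unexamined assumptions could be given more weight there than it deserves.

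**Working it through.** The documents give no first-stage figure, sample size or effect size for the IV analysis, so there is no stated number to reproduce. The check is one of logic, with two illustrations on **assumed** inputs.

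**1. Can homogeneity, as defined, be tested?** The definition asks "whether the IV-exposure association remains consistent across measured confounders of the exposure-outcome association". The instrument Z comes from past clients, the exposure from dispensations, and the measured confounders L are in Table 4. Add one term to a logistic first stage:

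logit P(SROM) = a + b·Z + c·L + d·Z·L

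On the log-odds scale, homogeneity as defined is d = 0, which is an ordinary test. Assumed inputs: 5,000 clients, 300 simulated data sets, Z uniform on 0 to 0.5, L present in 30%, a = −2.5, b = 4, c = 0.5, Wald test at two-sided 5%.

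| d | Slope where L = 1 (4 + d) | Rejected |
|---|---|---|
| 0 | 4 | 4% |
| −1 | 3 | 39% |
| −2 | 2 | 94% |
| −4 | 0 | 100% |

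The test keeps its level and detects sizeable differences. The rejection rates belong to these inputs. Smaller sub-populations would give less power, and a non-significant term would not prove homogeneity.

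**2. Does strong preference imply no defiers?** Take a simplified two-level instrument with a share pc of compliers and pd of defiers. The first-stage difference is pc − pd. With pc = 30% and pd = 5% it is 25 points, so the instrument is clearly relevant and defiers are still present. Monotonicity would be trivial only if preference settled every client's treatment. The article says that it largely does.

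**3. What can the data show about monotonicity?** Within a stratum the slope again reflects pc − pd.
- Clearly negative: defiers outnumber compliers there, which is evidence against monotonicity.
- Flat: the stratum may hold only clients whose treatment does not depend on the instrument, which is consistent with monotonicity. It may also hold equal shares of compliers and defiers.
- Positive: defiers are not excluded.

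A stratified first stage can therefore count against monotonicity but cannot confirm it.

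**4. What could defiers do to the estimate?** For a two-level instrument and a risk difference, with complier effect tc and defier effect td:

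IV estimand = (pc·tc − pd·td) / (pc − pd)

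Assume tc = −5 points and td = +5 points. For example, with pc = 0.20 and pd = 0.05: (0.20·(−5) − 0.05·5) / 0.15 = −1.25 / 0.15 = −8.3.

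| Defiers | pc = 20% | pc = 30% |
|---|---|---|
| 2% | −6.1 | −5.7 |
| 5% | −8.3 | −7.0 |
| 10% | −15.0 | −10.0 |

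If defiers share the complier effect (td = −5), the result is −5.0 in every cell and there is no bias.

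**The case against.** The strongest reply has five parts.

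- **The article hedges and consults.** It says that monotonicity is expected to hold, and it sends both assumptions to experts. This is true, but consultation does not correct a false statement about testability or supply a reason for monotonicity.
- **Monotonicity really cannot be verified.** This stands. The article is right on that half of its sentence, and the stratified first stage is only a partial falsification check.
- **The authors may have meant homogeneity over unmeasured confounders.** The definition would then be the sentence to correct. The two sentences still cannot both stand as written.
- **The design already separates clients by prior OAT.** Sub-populations (i) to (viii) do much of this. They do not compare first-stage slopes across other client characteristics.
- **The stakes are low.** This also stands. Table 5 lists IV estimation as a sensitivity analysis of the initiator effect only.

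A reader might also infer that the article's own account of SROM shows defiers. It does not. Selection on poor response, intolerance or QT risk produces clients who would get SROM, or not get it, whatever the prescriber's preference. That leaves monotonicity intact. Defiers require prescribers who rank clients differently. This is a fair inference where guidance rests on consensus, but no section says it. The guidance to "advise collaborative treatment selection based on client preferences, clinical judgement and contextual circumstances" dates from 2023, and accrual ended on December 31, 2022.

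**Conclusion.** The point holds in a limited form. By the article's own definition, homogeneity is testable with a model that is already planned, so the statement that it cannot be tested is wrong. *Trivially* is unsupported, because the reason given argues for relevance. The complier effect is stated without the condition on which it depends.

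These are two separate faults. A first-stage association that varies across covariates does not by itself invalidate a complier effect, so the missing homogeneity check does not show that effect to be wrong.

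The size of any bias is unknown. The figures of −5.7 to −15.0 points against a complier effect of −5 rest on invented shares and opposite effects, and on a two-level instrument with a risk difference. The article plans residual inclusion with a Cox model, so they do not carry over and serve only to show the direction of the problem. A reader should not infer that the planned estimate will be biased, that a flat slope reveals defiers, or that positive slopes everywhere would establish monotonicity.

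No primary estimate is affected. The correction is still worth making, because it changes what is done as well as how it is worded.

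**What to change.** 1. Correct the sentence on testability so that it agrees with the definition of homogeneity, and name the scale on which homogeneity is meant.
2. For each candidate instrument, pre-specify instrument-by-covariate interactions and stratum-specific first-stage slopes, reporting size, sign and confidence interval. Keep the list short: for example chronic pain, severe mental disorder, rural residence and calendar year from Table 4, plus prior OAT type where the sub-population does not already fix it.
3. State that this tests homogeneity as defined and is only a partial falsification check for monotonicity.
4. Replace *trivially* with a reasoned justification of why prescribers or facilities with a higher preference would not withhold SROM from clients who would get it elsewhere.
5. Make the complier interpretation conditional. Count a clearly reversed slope (interval excluding zero in the opposite direction) as evidence against it. Report a flat slope as a weak instrument in that stratum.
6. Do not limit the reported IV estimate to strata with a positive slope, because that would select populations on the estimated first stage.
7. Present any defier-bias figures as illustrations on assumed inputs.

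The cost is a few extra models and some rewording. The interpretation of one sensitivity analysis may become narrower. Study status and timeline says that no analyses have been run, so the checks can still be pre-specified.

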### Per-protocol analysis

We will conduct a per-protocol analysis to estimate treatment effects under sustained adherence at key dosing benchmarks, complementing the initiator effect.[86] To control the selection bias due to artificial censoring, we will consider two censoring models along with the propensity score models: (i) accounting for treatment switching, receipt of dose below key benchmark, and (ii) accounting for death, loss to follow-up, protocol violation by initiating pregnancy, dose taper, incarceration, or receipt of cancer or palliative care (see Table 3 for outcome specific censoring mechanism). Dose tapering is defined as two consecutive daily dose reductions without an intervening increase. Both censoring weights will be estimated using the approach described in the Initiator analysis section earlier. Final weights will be the product of the stabilized inverse probability of treatment weights at time zero and the post-baseline inverse probability of censoring weights, truncated at the 99th percentile. In the marginal structural model, we will apply a pooled logistic regression approach incorporating the final weights. The fitted model will be used to compute hazard ratios, risk differences, and risk curves. Compatibility intervals and curves will be computed using the approach described earlier. For sub-populations (ix) and (x), the censor-weighting approach will be similar, but we will apply a modified censoring mechanism as described in Table 3.

### Subgroup and sensitivity analyses

We will conduct a range of sensitivity analyses by restricting the study population and timeline to pre-COVID era, redefining key variables, and applying alternative estimation methods including hdPS estimation, IV estimation (see Table 5 for details).

Because fentanyl had already become the dominant opioid in the drug supply by 2017, it will not be feasible to examinae the effect of pre-fentanyl era on our findings. Relevant findings from each analytical approach will be presented in a forest plot. Any deviations from this protocol will be documented in the final reports.

### Ethics and Dissemination

This study uses de-identified administrative health data accessed under data-sharing agreements with the BC Ministry of Health and the Ministry of Mental Health and Addictions. Data were fully de-identified before being provided to the research team; no identifiable personal information was accessed. This initiative is categorized as a quality improvement project. The Providence Health Care Research Institute and the Simon Fraser University Office of Research Ethics reviewed the project, deeming it exempt according to Article 2.5 of the 2018 Tri-Council Policy Statement: Ethical Conduct for Research Involving Humans.[91] Because the study was conducted using de-identified administrative data and involved no direct contact with individuals, the requirement for informed consent was waived by the reviewing bodies. No participants, including minors, were contacted, and no written or verbal consent was sought or required. This study adheres to international guidelines, including Strengthening the Reporting of Observational Studies in Epidemiology guidelines,[92] and will be administered for ex post evaluation by a multidisciplinary scientific advisory committee. The results will be disseminated through peer-reviewed journals both electronically and in print, as well as at national and international conferences. This research aims to generate robust evidence for the effectiveness of SROM versus methadone and buprenorphine/naloxone dependent on one’s prior OAT experience, with the goal of improving[93] and life-saving[94] medications.

### Study status and timeline

The de-identified administrative health data from June 1, 2017 to December 31, 2022 has been obtained, but no analyses have been conducted to date. Data cleaning, cohort construction, and all planned analyses will begin following protocol approval and the study is expected to be completed within six months afterwards.

## Discussion

This study will generate population-level evidence on the comparative effectiveness of SROM, methadone, and buprenorphine/naloxone across ten clinically relevant sub-populations of both new and experienced OAT users. By emulating target trials with linked administrative data, we will estimate both the initiator and per-protocol effects of these medications. The application of marginal structural models, along with multiple sensitivity analyses, is designed to mitigate confounding by indication and other systematic biases that commonly affect observational OAT research. Findings will inform evidence-based refinement of OAT guidelines and support clinical decision-making in BC and other jurisdictions experiencing rising opioid-related harms.

A key limitation is the inability to directly measure several determinants of OAT selection, such as OUD severity, in-hospital OAT dispensing, non-medically attended overdoses, medication allergies or hypersensitivities, and changes in mental health symptoms, because they are not fully captured in administrative datasets. To reduce the resulting risk of residual confounding, we will use proxy measures available in administrative data in hdPS adjustments. Despite these constraints, the large population coverage, rigorous design, and comprehensive sensitivity analyses will provide robust and policy-relevant evidence on the comparative effectiveness of SROM relative to methadone and buprenorphine/naloxone.

### Patient and public involvement

Although no patients were directly engaged in designing this study, its conceptualization was shaped by previous interactions with local advocacy organizations representing individuals who use drugs and those accessing OAT.[95] Qualitative feedback on this and other related objectives outlined in the parent grant R01DA050629 was incorporated to prioritize this analysis, taking into account its potential impact on client engagement. The results will be disseminated to local advocacy groups after the analysis is completed.

## Figures and Tables

**Fig 1. F1:**
[figure not shown]
Construction of treatment episode for opioid agonist treatment for comparing slow-release oral morphine versus methadone and buprenorphine/naloxone

**Table 1: T1:** Key components of the emulated target trials on comparing the initiation of SROM versus methadone and buprenorphine/naloxone to treat people with opioid use disorder using the observational data

Protocol components	Hypothetical target trial	Emulation of the trial from BC health administrative data
Eligibility criteria	Adults aged 18 years or older who initiated OAT with MET, BNX, or SROM between June 1, 2017, and December 31, 2022. Individuals must not be pregnant or incarcerated and have no history of cancer or palliative care.	The same. To identify people who achieve better outcomes from SROM compared to MET and BNX, we will construct ten study populations to emulate the target trials (see Table 2 for details).
Treatment strategies	*For the study population (i) to (viii)* ITT: Initiating OAT with (1) MET, (2) BNX, and (3) SROM. PP: Receipt of at least 1 dispensation of optimal doses*: week 1: MET (≤40mg), BNX (≤16mg/4mg), SROM (≤240mg); weeks 2 through 3: MET (≥30 mg), BNX (≥12mg/3mg), SROM ((≥140mg); week 4 and beyond: MET (≥80mg), BNX (≥16 mg/4 mg), SROM (≥480 mg)[6] *For the study population (ix)* (1) Switching to SROM within 30 days of BNX initiation, (2) Staying on BNX. *For the study population (x)* (1) Switching to SROM within 30 days of MET initiation, (2) Staying on MET.	*For the study population (i) to (viii)* Treatment initiator effect and PP effect of the same strategies as proposed in the target trials. *For the study population (ix) and (x)* Same strategies as defined in the target trials.
Assignment procedures	Randomization. Prescribers, healthcare teams, and individuals are aware of the treatment status.	Individuals will be classified into treatment strategies based on dispensation records. Prescribers, healthcare teams, and individuals are aware of the treatment status.
Time zero	Date of randomization	Date of first OAT dispensation
Outcomes	Time to OAT discontinuation, along with the time to all-cause mortality and overdose-related acute care visit as the secondary outcomes.	Same.
Follow-up	Intention-to-treat (ITT): from time zero to outcome, death, loss to follow-up, 24 months after time zero, or December 31, 2022, whichever occurs first. Per-protocol (PP): additionally, we will assess adherence weekly and censor follow-up at protocol violation (see Table 3).	Same.
Causal contrasts	ITT for the sub-populations (i) to (viii) and PP for all.	Treatment initiator analysis for the sub-populations (i) to (viii), and PP for all.
Analysis plan	ITT: Hazard ratios will be estimated using Cox PH model. To obtain risk curves and risk differences at 24 months, we will estimate the baseline hazard and combine it with covariate effects to compute cumulative risks. To adjust for potential selection bias due to loss to follow-up, we will use inverse probability weighting (IPW) as a function of baseline and time-varying covariates. PP analysis: same except that individual are censored at non-adherence and uncensored individuals are assigned IPW that are a function of baseline and time-varying variables.	*For the study population (i) to (viii)* Initiator analysis: Marginal structural models with treatment weights from propensity scores models and censoring weights due to loss to follow-up. Weights will be estimated as a function of baseline and time-varying covariates. PP: Same as initiator analysis except potential pre- and post-baseline confounders that are associated with adherence to the treatment strategies will be included in the censoring models. *For the study population (ix) to (x)* Same PP analysis as applied to the study population (i) to (viii), except that individuals’ clone are used with a modified censoring mechanism (see Table 3).

* The optimal SROM doses are determined applying 1:6 MET-to-SROM conversion rate as per BC guidelines.[6]

**Table 2: T2:** Target study populations for comparative effectiveness analysis

Study population	Definition	Rationale
Incident users	(i) No history of OAT dispensation, dating back to January 1, 1996	To evaluate treatment outcomes among individuals initiating OAT for the first time
Prevalent new users	(ii) No dispensation for ≥5 days of methadone and SROM and ≥6 days for buprenorphine/naloxone	To capture repeated OAT attempts after a washout period, reflecting common real-world patterns.
Prevalent new users with past OAT experience	(iii) A history of methadone dispensation within past year of the index OAT episode	To assess individuals with recent prior experience of specific OAT which may influence current treatment response.
	(iv) A history of buprenorphine/naloxone dispensation within past year of the index OAT episode	
	(v) A history of methadone and buprenorphine/naloxone dispensation in past two years of the index OAT episode	
Prevalent new users who had previously completed OAT induction*	(vi) Completed methadone induction within past two year of the index OAT episode	To assess individuals recently stabilized on methadone and buprenorphine/naloxone, which may influence response to new treatment.
	(vii) Completed buprenorphine/naloxone induction within past two year of the index OAT episode	
	(viii) Completed methadone and buprenorphine/naloxone induction in past five years of the index OAT episode	A history of completing both inductions may reflect complex needs or higher tolerance, informing comparative effectiveness.
Individuals initiated treatment with buprenorphine/naloxone	(ix) Individuals initiated OAT with buprenorphine/naloxone will be included. Switching to SROM within 30 days of initiation will be compared with staying on buprenorphine/naloxone in a two-arm study.	Early switching within buprenorphine/naloxone episode may indicate suboptimal response or poor tolerability.
Individuals initiated treatment with methadone	(x) Individuals initiated OAT with methadone will be included. Switching to SROM within 30 days of initiation will be compared with staying on methadone in a two-arm study.	Early switching within methadone episode likely reflects adverse effects such as sedation, emotional blunting, or QT-related cardiac risk.

* Induction completion is defined as no dose change within at least two consecutive weeks.

**Table 3. T3:** Censoring indication in the primary and secondary analyses for comparing slow-release oral morphine versus methadone and buprenorphine/naloxone.

	OAT discontinuation		All-cause mortality		Overdose-related acute-care visits	
	Initiator	Per protocol	Initiator	Per protocol	Initiator	Per protocol
OAT discontinuation	outcome	outcome				
End of study ^a^	C_1_	C_1_	C_1_	C_1_	C_1_	C_1_
Death	C_2_	C_2_	outcome	outcome	C_2_	C_2_
Loss to follow-up	C_2_	C_2_	C_2_	C_2_	C_2_	C_2_
Deviation from inclusion/exclusion criteria		C_2_		C_2_		C_2_
Deviation from the protocol		C_3_		C_3_		C_3_
Treatment switch		C_3_		C_3_		C_3_
The overdose-related first acute-care visit					outcome	outcome

a. end of study follow-up is either Dec 2022 or 24 months from time zero, whichever occurs earlier C_1_, C_2_, and C_3_ indicate different censoring mechanism: C_1_: censoring due to end of study follow-up; C_2_: censoring due to death (not the all-cause mortality outcome), loss to follow-up, deviation from the trial exclusion criteria such as initiation of pregnancy, incarceration, dose taper, cancer or palliative care, leaving out of BC. Dose taper will be defined as two consecutive daily dose decreases (without intervening increase); C_3_: censoring due to deviation from the dosing protocol as mentioned in the key measures section, including treatment switching. Censoring for violating dosing protocols will not be applied to the study sub-populations (ix) and (x), as defined in Table 2. For the clone designated for switching to SROM in these sub-populations, individuals will be censored at day 30 if they remain on the initial OAT beyond 30 days, but will not be censored if they switch to SROM within 30 days of initiation; Separate censoring models will be used for C_2_ and C_3_.

**Table 4. T4:** Time fixed and time-varying covariates to estimate the inverse probability of treatment and censoring weights

Variable	Category	How the variable is defined and measured
*Socio-demographic factors*		
Age	Continuous	Based on birth date information from the client registry.
Sex	Male/Female	Based on medical records that record sex.
Living in rural region	Yes/No	Based on the population of the assigned local health area[65]
Homelessness/unstable housing in past 5 years^‡^	Past year, Past 1–5 years, Never/>5 years	Defined through International Classification of Diseases (ICD) 10: Z59.0, Z59.1 from physician billing or hospital discharge records or 3 consecutive records of no fixed address from Social Development and Poverty Reduction (SDPR)
Incarcerated in past year^‡^	Yes/No	Admission to BC correctional facilities and identified through records in the past year from the provincial corrections database.
Receipt of income assistance in the past year^‡^	Yes/No	Identified through records in SDPR and PharmaCare plan information on medication dispensations, using records within the past year.
Calendar year of time zero	2010 to 2022	Determined based on the dispensation date from PharmaNet.
*Comorbidity*		
Severe mental disorder (ever)^‡, a^	Yes/No	Includes major depressive disorder, bipolar disorder, and schizophrenia, and identified through ICD codes if diagnosed ever and updated if diagnosed during episode follow-up.
Alcohol use disorder (ever)^‡, a^	Yes/No	Identified through ICD codes and DIN/PIN, if diagnosed ever and updated if diagnosed during episode follow-up.
Hepatitis C virus (ever) ^‡, a^	Yes/No	Identified through ICD codes if diagnosed ever and updated if diagnosed during episode follow-up.
Asthma (ever)^‡, a^	Yes/No	Identified through ICD codes* and DIN/PIN within the past year, updated during the follow-up.
Chronic pain in past year^‡, a^	Yes/No	Identified through ICD codes within the past year, updated during follow-up.
Chronic obstructive pulmonary disease^‡, a^	Yes/No	Identified through ICD codes within the past year, updated during the follow-up.
Charlson comorbidity index in past year^‡^	0 and above	Using the Charlson comorbidity index[66] and hospitalization records within the past year, and updated during the follow-up.
Dispensations of psychiatric or sedative medication in the past month^‡, a^	Yes/No	Identified through DIN/PIN of dispensations in the past 30. Updated during the follow-up.
*Factors related to OAT experience*		
Dispensations opioid other than OAT in the past month^‡, a^	Yes/No	Identified through DIN/PIN and a case-finding algorithm used prior[67] and updated during the follow-up.
Received prescription opioids other than OAT prior to OUD diagnosis ^a^	Yes/No	Identified through DIN/PIN and a case-finding algorithm used prior[67] and updated during the follow-up.
Treated tobacco use disorder in past year^‡, a^	Yes/No	Based on ICD-10 codes and indication of nicotine replacement therapy in PharmaNet
Attachment to the prescriber ^‡, a^	Yes/No	Identified based on billing history from the physician. More than 50% of physician billing attributed to the prescriber in the past 12 months
Funding of prescribers who initiated OAT: alternative payment plan	Yes/No	Alternative payment plan indicated by the absence of a medical services plan billing record (capturing fee-for-service billing) at initial OAT dispensation.
Urine drug test in the past week^‡^	Yes/No	Receipt of urine drug test from physician billing records
Practice size^‡^	Large, medium, small	Determined by network analysis; number of unique OAT clients in past 12months. Large for >300 clients, medium for 16–300 clients and small for ≤15 clients.
*COVID-19 related factors*		
Virtual care^‡^	Yes/No	Virtual care indicated in physician billing records.[68,69]
OAT pharmacy delivery^‡^	Yes/No	Indication of delivery of OAT in PharmaNet
Receipt of prescriber safer supply (PSS) ^‡^	Yes/No	Concurrent PSS dispensations in PharmaNet.[70]

DIN: drug identification number

PIN: product identification number;

‡ Time dependent variable will be updated weekly;

a. ICD codes for each condition and DIN/PINs for different medications can be found elsewhere.[58]

**Table 5: T5:** Proposed subgroup and sensitivity analysis

Proposed sensitivity analysis	Rationale	Initiator/PP
